## Abstract

**Background:**

With potent antiretroviral drugs, HIV infection is becoming a chronic disease. Emergence of comorbidities, particularly cardiovascular disease (CVD) has become a leading concern for patients living with the infection. We hypothesized that the chronic and persistent inflammation and immune activation associated with HIV disease leads to accelerated aging, characterized by CVD. This will translate into higher incidence rates of CVD in HIV infected participants, when compared to HIV negative participants, after adjustment for traditional CVD risk factors. When characterized further using cardiovascular imaging, biomarkers, immunological and genetic profiles, CVD associated with HIV will show different characteristics compared to CVD in HIV-negative individuals.

**Methods/design:**

The Canadian HIV and Aging cohort is a prospective, controlled cohort study funded by the Canadian Institutes of Health Research. It will recruit patients living with HIV who are aged 40 years or older or have lived with HIV for 15 years or more. A control population, frequency matched for age, sex, and smoking status, will be recruited from the general population. Patients will attend study visits at baseline, year 1, 2, 5 and 8. At each study visit, data on complete medical and pharmaceutical history will be captured, along with anthropometric measures, a complete physical examination, routine blood tests and electrocardiogram. Consenting participants will also contribute blood samples to a research biobank. The primary outcome is incidence of a composite of: myocardial infarction, coronary revascularization, stroke, hospitalization for angina or congestive heart failure, revascularization or amputation for peripheral artery disease, or cardiovascular death. Preplanned secondary outcomes are all-cause mortality, incidence of the metabolic syndrome, incidence of type 2 diabetes, incidence of renal failure, incidence of abnormal bone mineral density and body fat distribution. Patients participating to the cohort will be eligible to be enrolled in four pre-planned sub-studies of cardiovascular imaging, glucose metabolism, immunological and genetic risk profile.

**Discussion:**

The Canadian HIV and Aging Cohort will provide insights on pathophysiological pathways leading to premature CVD for patients living with HIV.

**Electronic supplementary material:**

The online version of this article (10.1186/s12879-017-2692-2) contains supplementary material, which is available to authorized users.

## Background

As a result of recent advances in antiretroviral therapy (ART), HIV-infected individuals live longer, with an estimated life expectancy that ranges from 20 to 50 years following infection, and in some cases could reach normal life expectancy [1–3]. Factors that impact on longevity include: the age at infection, the nadir CD4 cell count, the time spent with CD4 counts >500 cells/mm^3^, and other variables [1, 3–8]. In 2015, it was estimated that 50% of HIV-infected persons were >50 years of age, making them susceptible to diseases related to aging [2, 3, 9]. Furthermore, some age-related diseases may be overrepresented in the HIV population, and appear approximately 5 to 10 years earlier than in the general population [10–12]. This has led to the concept of “premature aging” in HIV-infected individuals [13, 14]. This term is controversial, since not all HIV-infected individuals show signs of accelerated aging, and not all components of the aging phenotype have been observed prematurely in the HIV-population. Co-morbid conditions of particular concern include cardiovascular diseases (CVD), the metabolic syndrome (MetS), early onset of osteoporosis, and renal impairment. The pathophysiological processes leading to these phenotypes are complex and not completely understood.

Several hypotheses have been put forward to try to explain premature aging: mitochondrial toxicity, immunodeficiency, antiretroviral toxicity, lifestyle, and a chronic state of immune activation [15–18]. The consequence of chronic immune activation is the development of a senescent immune phenotype, with impaired thymic function, reduced T-cell repertoire and regeneration potential and T cell exhaustion, similarly to what is observed in aging [19, 20].

Large cohort studies have shown an increased risk of CVD in HIV-infected individuals. Compared to age and sex matched controls, we found a hazard ratio for myocardial infarction associated with HIV infection of 2.13 (95% confidence interval [CI] 1.69–2.63) in local data from a Québec administrative database [21]. In the international Data Collection on Adverse Events of anti-HIV Drugs (D:A:D) cohort including 33,347 HIV positive patients, an overall rate of myocardial infarction of 3.48/1000 person-years was reported [22, 23]. A meta-analysis of observational and randomized controlled trials reporting CVD showed that the relative risk of CVD was 1.61 (95% CI 1.43–1.81) among ART-naïve HIV-infected compared with HIV-uninfected people [24, 25].

The overrepresentation of traditional cardiovascular risk factors, particularly smoking, in HIV-infection population can explain part of the excess CVD risk [26]. However, traditional risk factors may not explain the totality of the excess risk. We wish to further characterize the causative pathways and identify predictors of this premature CVD associated with HIV infection. Through better understanding of the particular physiopathology underlying CVD in HIV, our ultimate aim is to prevent negative outcomes and optimize primary care interventions. This study will focus on identifying the type, frequency and determinants of premature CVD in HIV-infected individuals.

### Study hypothesis

The chronic and persistent inflammation associated with HIV disease leads to accelerated aging, characterized by premature CVD, altered metabolism and immune senescence. This will translate into higher incidence rates of CVD in HIV infected participants, when compared to HIV negative participants, after adjustment for traditional CVD risk factors. When characterized further using cardiovascular imaging, biomarkers, immunological and genetic profiles, CVD associated to HIV will show different characteristics compared to CVD in HIV-uninfected individuals.

## Methods/design

### Study design

This is a controlled, prospective cohort study. Pre-planned sub-studies will be nested within the cohort. The exposure of interest for the main cohort and all sub-studies is HIV infection.

### Setting

This is a multicenter study, conducted in 10 Canadian centers.

### Primary outcome

Incidence of CVD, defined as incidence of any of the following conditions: MI, coronary revascularization, stroke, transient ischemic attack, hospitalization for angina or congestive heart failure, revascularization or amputation for peripheral artery disease, or cardiovascular death.

### Secondary outcomes

Secondary outcomes are: i)incidence of all-cause mortality, ii)incidence of major adverse cardiac and cerebrovascular events (MACE - composite outcome composed of cardiovascular death, MI, coronary revascularization or stroke), iii)incidence of individual components of the primary outcome, iv)incidence of the metS, v)incidence of type 2 diabetes, vi)incidence of renal failure, vii)incidence of abnormal bone mineral density and body fat distribution.

Complete definitions of outcomes are available in Additional file 1.

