### Study visits

Patients will be followed yearly for 3 years (baseline, year 1 and year 2), then have additional visits at years 5 and, depending on their recruitment date, at year 8. At each study visit, participants will complete study questionnaires, have a complete medical history and physical examination by a physician, have a panel of blood tests and an electrocardiogram. Twice during the study (year 1 and final year), participants will also undergo a dual energy X-ray absorptiometry to measure bone mineral density. In addition, all participants will be invited to contribute to a research blood bank, to which they will contribute serum and cells. Depending on availability at research sites, participants will also be invited to undergo leukapheresis, to maximize the number of white blood cells available in the biobank. Throughout follow-up, participants’ eligibility to the pre-planned sub-studies will be assessed, and patients will be offered participation in the sub-studies (presented below). Additional files 2 and 3 present tasks performed at each study visit and list of blood tests obtained, respectively.

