### Statistical considerations

#### Power calculation

Based on data from both our local HIV database and our pilot study [27, 28], we expect the HIV positive population to be 80% male, with a mean age of 50 years at the beginning of the study. Based on data from the Framingham study, expected rates of our primary outcome in HIV-negative participants are 10/1000 person-years for men and 4/1000 person-years for women in the 45–54 age group [29]. The rates more than double for the 55–64 age group [29]. Accordingly, we assume the overall CVD incidence rate in HIV-negative controls will range between 8/1000 PY and 12/1000 PY. Analysis for the primary outcome will be limited to subjects who are free of CVD at baseline. We expect that, at baseline, up 10% of HIV- and 15% of HIV+ subjects will have prevalent CVD [29]. Finally, we assume that an average CVD-free subject will contribute 4 years of follow-up (of the maximum potential follow-up of 5 years). Under these assumptions, the recruitment of 1000 subjects in each group (implying that 900 HIV- and 850 HIV+ subjects will be free of CVD at baseline, contributing 3600 and 3400 PY of follow-up) will yield 80% power with alpha = 0.05 to detect hazard ratios of 1.72 to 1.90 for the primary composite outcomeof CVD. These risk increases are clinically plausible and are actually lower than the more than 2-fold (HR > 2.0) increases in the risk of major CVD events associated with HIV infection [30]. Some studies have reported higher HRs for specific sub-populations or CVD events, e.g. HR 4.0 for risk of stroke among younger subjects [31]. All sample size calculations were done with the PASS software [32].

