### Primary outcome

Longitudinal analyses of the CVD incidence/prospective analysis: This analysis will use prospective data and will focus on time until occurrence of the first incident CVD event, as defined by the composite outcome described above. It will be limited to subjects without a history of CVD at cohort entry. Analyses will employ time-to-event statistical methods including Cox proportional hazards (PH) model [33] and its flexible extensions. Time 0 will be defined as the cohort entry and subjects who do not develop CVD during the follow-up will be right-censored at the earliest of times of: loss to follow-up, administrative end of the study or a non-CVD death**.** In all models, the binary indicator of HIV infection will be the main ‘exposure’ and its effect on the risk (hazard) of incident CVD will be adjusted for “standard confounders”: age, sex, ethnicity, education, income, and illicit drug use. However, two different types of models will handle differently the CVD risk factors, to provide a better understanding of the mechanisms through which HIV infection may affect future CVD risks. The first model will adjust the effect of HIV for only the baseline values of CVD risk factors, in addition to “standard confounders”. This will allow us to estimate and test the potential differences in CVD incidence between HIV+ vs. HIV- individuals who had the same initial values of common CVD risk factors, at cohort entry. In contrast, the second model will adjust for the up-dated values of CVD risk factors, modeled by time-varying covariates, representing the most recent value observed until a given date during the follow-up. This model will permit testing if there is a ‘residual’ impact of HIV infection that is *not* mediated through longitudinal changes in common CVD risk factors. The independent association between HIV and CVD incidence will be then estimated through the adjusted HR, with 95% confidence intervals (CI). In both analyses the proportional hazards assumption we will be tested using a flexible extension of the Cox model [34, 35].

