### Secondary outcomes

Incidence rates of secondary outcomes will be modeled as described for the primary outcome, through adjusted multivariable survival models.

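### Bone mineral density is measured twice on a continuous scale but analysed only as incident abnormality, which can cost much of the power to detect a small HIV difference in bone loss

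*Protocol article*

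**What the plan says.** In the protocol article, the last item under Secondary outcomes (Methods/design) is "incidence of abnormal bone mineral density and body fat distribution". No cut is given there; the article says "Complete definitions of outcomes are available in Additional file 1", and that file is not shown.

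The analysis is stated in one sentence under Statistical analysis, Secondary outcomes: "Incidence rates of secondary outcomes will be modeled as described for the primary outcome, through adjusted multivariable survival models". No exception is made for bone density. The primary model that it points to excludes people who already have the condition, and states "Time 0 will be defined as the cohort entry".

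The measurement is described under Study visits: "Twice during the study (year 1 and final year), participants will also undergo a dual energy X-ray absorptiometry to measure bone mineral density". Participants "have additional visits at years 5 and, depending on their recruitment date, at year 8", so the scans lie about 4 years apart (5 - 1) or 7 years apart (8 - 1).

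**The concern.** A continuous reading taken twice is reduced to one yes/no crossing. Information is lost in two places:

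- A participant already beyond the cut at the first scan cannot have an incident event, so further bone loss in that person does not count.
- Among the rest, mainly those who start near the cut can cross it. Loss in everyone else is measured and then ignored.

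A modest HIV effect on mean bone loss therefore moves the event proportion very little. The Background names early osteoporosis among the comorbidities of particular concern, and bone density is a pre-planned secondary outcome. The risk is that a real but small difference, which the planned scans could show, is reported as no difference.

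**Working it through.** **The plan's own power figure.** The main cohort has one, for the primary outcome (80% power, hazard ratios 1.72 to 1.90). It reproduces:

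- At 8/1000 person-years and HR 1.90: events = 3600 × 0.008 + 3400 × 0.008 × 1.90 = 80.5. Freedman: √80.5 × 0.90/2.90 - 1.96 = 0.82, power 79.5%.
- At 12/1000 and HR 1.72: events = 113.4. √113.4 × 0.72/2.72 - 1.96 = 0.86, power 80.5%.

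No such figure exists for bone density, so everything below is assumption.

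**Assumed inputs.** The plan is for "the recruitment of 1000 subjects in each group"; I take 600 or 800 per group with both scans. First-scan T-score: mean -0.3 or -0.8, SD 1.1. Change: control mean -0.1, residual SD 0.3 or 0.5. Abnormal: T-score at or below -1.0 or -2.5.

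**Effect size.** The HIV difference in loss is set so that the continuous analysis has about 80% power: δ = 2.8 × SD × √(2/n). The smallest is 2.8 × 0.3 × √(2/800) = 0.042; the largest is 2.8 × 0.5 × √(2/600) = 0.081.

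**One case in full** (n = 800, mean -0.8, SD of change 0.5, cut -1.0, equal starts):

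1. δ = 2.8 × 0.5 × √(2/800) = 0.07.
2. Already abnormal at the first scan: Φ((-1.0 + 0.8)/1.1) = 43%. About 458 per group remain at risk.
3. Probability of crossing by the second scan, given a first value above the cut (simulated): 15.5% in controls, 18.0% in HIV-positive participants.
4. Standard error = √(0.168 × 0.832 × 2/458) = 0.0247; z = 0.0253/0.0247 = 1.02.
5. Power = Φ(1.02 - 1.96) = about 17%, against 80% for the continuous analysis.

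**Over the grid:**

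| Situation | Continuous | Incident, cut -1.0 | Incident, cut -2.5 |
|---|---|---|---|
| Equal starts, δ 0.04-0.08 | about 80% | 12-19% | 6-13% |
| Equal starts, δ 0.07-0.13 | about 99% | 24-39% | 8-24% |
| Equal starts, δ 0.2 | nearly 100% | 72-96% | 31-75% |

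If HIV-positive participants start 0.3 T-score lower and δ is 0.04-0.08, incident abnormality has 32-67% power across both cuts. Part of that gain reflects where the groups start, because more HIV-positive participants sit just above the cut. It is not all evidence about loss between the scans.

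**Cross-check with other assumptions.** First reading standard normal, mean change -0.15 SD, 800 per group, cuts that put 5% to 50% of people in the abnormal category, equal starts: power falls from 80% to 8-13% (SD of change 0.3) or 13-19% (SD of change 0.5).

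**Does the survival model recover the loss?** Hardly. With two scans the crossing time is known only to lie between them, and status at cohort entry is not measured because the first scan is at year 1. Event times add little to the crossing proportion, so comparing proportions is a fair stand-in, although it leaves out the planned covariate adjustment.

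**The case against.** **The category has a clinical basis.** The other secondary outcomes also concern incident events or conditions, and the article claims no power for this one. This stands. It is a reason to keep incident abnormality, and no reason to leave out a continuous analysis of the same scans.

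**The definitions are in a file not shown.** True, so the cut itself cannot be criticised, and a fuller plan may already contain a continuous analysis. But that file is cited for definitions of outcomes, and the article's own analysis sentence covers all secondary outcomes without exception.

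**The size depends on the inputs.** This stands. A reader who saw only the 80% and 99% rows with equal starts might infer a loss of at least 60 percentage points. The documents do not support that as a minimum. They admit people with 15 or more years of infection, so a deficit at the first scan is plausible, and with one the gap narrows. It also narrows for larger differences.

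**Adjusting for the year-1 value is not harmless.** In a non-randomised cohort, it sets aside any HIV-related deficit already present at that scan. This stands and shapes the fix.

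**Body fat.** A reader might infer that body fat distribution is also a DXA measure read twice. Study visits ties DXA to bone density only, the article names no method for fat distribution, and it is unclear whether the outcome's wording makes fat an abnormal/normal category at all. That extension is not supported.

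**Conclusion.** The point holds for bone mineral density. The article states a categorical survival analysis for a continuous measure read twice. Under the assumed inputs, an HIV difference in loss of about 0.04 to 0.08 T-score that is detectable with 80% power on the continuous scale has about 6-19% power as incident abnormality with equal starts, and about 32-67% if HIV-positive participants start 0.3 lower. At a difference of 0.2 with equal starts, the loss is modest at a cut of -1.0 and still substantial at -2.5. None of these inputs comes from the documents. The direction of the loss is robust under equal starts; its size is not fixed. Nothing here shows the clinical category to be wrong, or reaches body fat as the article describes it.

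**What to change.** Under Statistical analysis, Secondary outcomes, add for bone mineral density a continuous analysis of the two scans by HIV status. Use either annualised change or a mixed model of both readings, adjusted for time between scans and the plan's standard confounders. Report the HIV-positive minus HIV-negative difference with a 95% confidence interval. Also report the difference at year 1, so that a deficit already present at the first scan is not lost. Keep incident abnormality alongside as the clinical outcome.

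Extend this to body fat distribution only if the full protocol confirms a repeated continuous measurement.

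Cost: a sentence or two of analysis wording and one more analysis, with no new data. The added estimate is a mean difference, which is less directly clinical than a category; the retained incidence analysis covers that.

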### Study participants

***HIV-infected:*** All individuals living with HIV (as defined by a positive serology for HIV) followed in the HIV clinics of the participating centers, as well as all newly infected or newly diagnosed participants meeting inclusion criteria will be offered to take part into the cohort. ***HIV-uninfected***: HIV-seronegative individuals will be selected from among i)healthy individuals from the general population, reached through publicity campaigns, HIV prevention clinics and participating community members. ii) HIV-uninfected individuals followed at the participating clinics and hospitals. The HIV-negative participants will be frequency matched for age, sex and smoking status, but no individual matching will be done. This will be achieved through periodic comparisons of age and sex distributions of the HIV-positive and HIV-negative participants (every 6 months during the enrollment period) and adjustments in study publicity targeting the HIV-negative group.

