### Inclusion criteria

HIV-infected participants must be ≥40 years of age or have HIV infection lasting for at least 15 years (proven by anti-HIV antibody test) at the time of enrollment, be able to provide informed consent and have a life expectancy of at least 1 year. Control group participants must be ≥40 years of age, be able to provide informed consent and have a life expectancy of at least 1 year.

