### Sensitivity analysis

Retrospective and prospective data analysis: In another model, we will not exclude patients with presence of CVD at baseline. The rationale for this is as follows: if HIV patients experience premature CVD, as we hypothesize, and since HIV patients enter the cohort after varying durations of HIV infection, the risk of CVD associated with HIV might be underestimated if patients with prevalent CVD are excluded from the analysis, i.e.: we would “miss” the earlier events occurring in the HIV infected patients before their entry into the cohort.

In this model, HIV infection will remain the main ‘exposure’, but time 0 will be defined as birth date. HIV infection will be coded in a time-dependent manner: “0” for the time before HIV infection in HIV-infected participants and for HIV-negative controls throughout follow-up, and “1” following first HIV diagnosis in HIV-infected individuals. Incidence of CVD will be modeled using time-to-event statistical methods, as described above, with the first incidence of CVD occurring before cohort entry for patients with prevalent CVD at baseline. Dates of CVD occurrence for patients with prevalent CVD at baseline will be obtained retrospectively (at the baseline visit, through pre-planned data collection for complete medical history). Patients will be right-censored at the earliest of times of: loss to follow-up, administrative end of the study or a non-CVD death**.**

Effect of HIV on the risk (hazard) of incident CVD will be adjusted for “standard confounders”: sex, ethnicity, education level, and income (coded as constant over time), as well as smoking, illicit drug use, sedentary lifestyle, and BMI (coded as time dependent variables). Period of prospective cohort participation (coded in a time-dependent fashion as 0/1) will also be added as a potential confounding variable, as being prospectively followed and assessed for CVD will be likely to increase CVD detection.

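### Recruiting one of the two control sources as healthy can bias the sensitivity analysis that counts CVD before cohort entry

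*Protocol article*

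**What the plan says.** The protocol article names two sources of HIV-negative participants (Study participants). The first is "healthy individuals from the general population, reached through publicity campaigns, HIV prevention clinics and participating community members". The second is "HIV-uninfected individuals followed at the participating clinics and hospitals", with no health qualifier. No split between the two is given. People with HIV at the participating clinics are all offered enrolment if they meet the inclusion criteria, again with no health qualifier.

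The Inclusion criteria do not repeat the qualifier: "Control group participants must be ≥40 years of age, be able to provide informed consent and have a life expectancy of at least 1 year". The Discussion also describes general-population recruitment without it. The Power calculation expects that "up 10% of HIV- and 15% of HIV+ subjects will have prevalent CVD".

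The primary analysis is limited to subjects without a history of CVD at entry, in both groups. The Sensitivity analysis section does the opposite: "In another model, we will not exclude patients with presence of CVD at baseline". Time 0 is birth, HIV is coded as time-dependent from diagnosis, and a participant with prevalent CVD has an event at the retrospectively obtained date. An indicator for the period of prospective participation is added because detection is likely to be better after entry. The stated reason for this model is that excluding prevalent cases might underestimate the HIV effect.

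**The concern.** A site that follows the Study participants text would advertise for healthy people. A site that follows the Inclusion criteria would not. The difference decides who enters the control group.

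In the sensitivity model CVD before entry is the outcome. If *healthy* is taken to mean free of CVD, controls from that source are enrolled because they have had no event, and their decades before entry count as event-free time at risk. People with HIV face no such selection. The resulting bias raises the HIV hazard ratio, which is the direction the model was added to look for, so a reader could not tell the artefact from support for the hypothesis.

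**Working it through.** **1. The plan's own figure.** The inputs are "900 HIV- and 850 HIV+ subjects will be free of CVD at baseline, contributing 3600 and 3400 PY of follow-up", and "we assume the overall CVD incidence rate in HIV-negative controls will range between 8/1000 PY and 12/1000 PY". Expected events are 3600 × rate in controls and 3400 × rate × HR in HIV+. Power for a two-sided Wald test at 0.05 is Φ(ln HR / √(1/e0 + 1/e1) − 1.96).

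- Rate 8/1000, HR 1.90: e0 = 28.8, e1 = 51.7, total 80.5; power 78.8%.
- Rate 12/1000, HR 1.72: e0 = 43.2, e1 = 70.2, total 113.4; power 80.1%.

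The stated range of 1.72 to 1.90 reproduces. It concerns CVD-free subjects only, so this point does not affect it.

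**2. Weight of pre-entry events in the sensitivity model.** On the plan's assumptions, 10% and 15% of 1000 give 100 + 150 = 250 prevalent cases. Their share of all events is 250/(250 + 80.5) = 76% to 250/(250 + 113.4) = 69%. This uses the planned prevalences and hazard ratios, so it shows the order of importance and is not a null scenario.

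**3. Is the 10% compatible with CVD-free volunteers?** If the general-population source had no prior CVD and supplied a share f of controls, the clinic and hospital source would need prevalence 0.10/(1 − f) to reach 10% overall: 13% for f = 0.25, 20% for f = 0.50 and 40% for f = 0.75.

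**4. Null simulation of the sensitivity model.** The true HIV hazard ratio is 1.0 and the model is Cox from birth with time-dependent HIV and the time-dependent prospective-period indicator. There are 1000 subjects per group and 60 to 80 replicates per scenario. These inputs are assumptions, not in the document: entry age normal with mean 50 and SD 7, limited to 40–75; cumulative CVD hazard −ln(0.90) × (age/50)^5; HIV diagnosis 0 to 25 years before entry; 4 years of follow-up for everyone; no other covariates. Prior CVD in the HIV+ group is then 11–12%. In the table, clinic and hospital controls carry average risk.

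| Share of controls selected CVD-free | Null HR | False finding of HR > 1 |
|---|---|---|
| 0 | 1.01 | about 0% |
| 0.25 | 1.17 | 28% |
| 0.50 | 1.37 | 72–78% |
| 0.75 | 1.7 | 96–97% |
| 1 | 2.2 | 100% |

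Separate runs at one half gave 1.34 to 1.40. With a higher baseline prevalence setting (15%) the results were 1.38 at one half and 2.16 at all. The prospective-period indicator was in the model throughout and did not remove the bias. The primary-analysis hazard ratio stayed at about 1.0 (0.96 to 1.07).

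**5. The same model with more CVD among clinic and hospital controls.**

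- Half selected CVD-free, overall control prevalence 11%: HR 1.03, 4% false findings.
- Three quarters selected CVD-free, overall control prevalence 9%: HR 1.14, 20% false findings.
- Half selected CVD-free, 20% prior CVD in the clinic source (10% overall), with underlying CVD of about 12% by age 50: HR 1.16.

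**The case against.** The strongest reply is that *healthy* is loose wording that separates community volunteers from clinic patients. The Inclusion criteria, where eligibility is fixed, contain no CVD exclusion, and the Discussion drops the word. This stands as far as it goes: nothing in the article defines *healthy* as CVD-free, so the bias is conditional on how sites apply it.

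A reader might infer that the 10% prevalence assumption contradicts the recruitment of healthy controls. It does not. The figure is an upper bound for all controls together, and the clinic and hospital source can supply the cases.

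A reader might also infer that the sensitivity analysis must show an HIV effect by construction. The documents do not support that either. People under clinic or hospital care may have more CVD than average, and step 5 shows that this can almost cancel the bias. The cancellation would, however, depend on two unplanned selections offsetting each other, with a source split that is not stated.

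Finally, a crude comparison of pre-entry cumulative hazards looks larger. With 15% in HIV+ and 7.5% in controls it is −ln(0.85)/−ln(0.925) = 0.1625/0.0780 = 2.08. That is not what the model estimates, because HIV is coded 0 before diagnosis.

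**Conclusion.** The point holds in conditional form. The qualifier applies to one control source only, is undefined, and has no counterpart in the HIV+ group or in the Inclusion criteria. If it is applied as free of CVD, the sensitivity model selects on its own outcome in the unexposed group only. With average CVD risk in clinic and hospital controls, the null hazard ratio is then about 1.2, 1.35 and 2.2 when a quarter, half and all of the controls are selected in this way. With enough extra CVD in the clinic and hospital source it can be near 1.0. These sizes rest on the assumed age, hazard and diagnosis-time distributions, and on a source split that the article does not give.

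The primary analysis and the power figure are essentially unaffected. What is at risk is the use of the sensitivity result as evidence that the primary analysis underestimates the HIV effect.

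**What to change.** Delete *healthy* from the Study participants section and state that CVD history plays no part in inviting or enrolling controls from either source, in line with the Inclusion criteria. The cost is a wording change and slightly more controls excluded from the primary analysis for prevalent CVD, within the 10% already allowed for (900 of 1000 CVD-free).

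If some controls were already recruited as healthy, report the sensitivity result as possibly biased by control selection, and do not present it as evidence that the primary analysis underestimates the effect.

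Do not repair the model by starting risk time at cohort entry for the general-population source alone. All pre-entry control experience would then come from clinic and hospital controls. In null simulations (25 replicates) this moved the hazard ratio from 1.40 to 0.99 when those controls had average risk. It moved it from 1.16 to 0.83 when half of controls were CVD-free and the clinic source had 20% prior CVD, and from 1.13 to 0.62 with three quarters and 40%. The bias can therefore be reversed instead of removed.
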